### Concomitant treatments

Routine medication for maintenance HD will be continued. The medication regimen will be recorded at every visit, and participants will need to inform the study assistant of any changes to their medication, supplements, and even exercise. Additional acupuncture, herbal prescriptions, or other interventions by other TCM practitioners will not be permitted during the treatment period.

### Randomization and allocation

The participants will be allocated into group A (*n* = 20) or group B (*n* = 20) according to a randomized list generated in Microsoft Excel 2016. Participants will be coded with identification numbers to guarantee confidentiality during data analysis. The physicians will have no access to the sequence, and the investigators will distribute the drugs. All members of the research team will be explicitly instructed not to inform the participants of their allocations. The clinical outcomes assessor will be blinded to the allocations to decrease the risk of observer bias. Participants' files will be kept in a box in a locked cabinet only accessible by an assistant until the end of the study.

Participants will be coded with identification numbers to guarantee confidentiality during data analysis. Participants' files will be stored in a secure room in the TCM Education Research Office, Rehabilitation Building of Kaohsiung CGMH.

### Outcome measurement

The subjects will be assessed five times: prior to the study, at 4 weeks (at the end of period I), at 6 weeks (at the beginning of period II), at 10 weeks (at the end of period II), and at follow-up (2 weeks after the trial period ends). A research assistant will be trained to ensure the accuracy of outcome assessments and data collection.

#### Primary outcome

The primary outcome used in this study will be the Kidney Disease Quality of Life 36-Item Short-Form Survey (KDQOL-36), a self-report measure developed for health-related concerns of individuals who visit dialysis facilities for treatment (29). The KDQOL-36 is available in English and was translated into Mandarin Chinese by the RAND Corporation (see: http://www.rand.org/health/surveys_tools/kdqol.html). The instrument is composed of 12 general health items and 24 kidney-specific items. The items on general health are summarized into a Physical Component Summary (PCS) score and a Mental Component Summary (MCS) score. The 24 kidney-specific items comprise three scales: symptoms and problems, burden of kidney disease, and effects of kidney disease (12, 4, and 8 items, respectively). The raw scores are transformed into a linear range of 0–100, where higher scores indicate better QOL (30).

#### Secondary outcomes

Secondary outcome measures will include arm motor function evaluated with the Fugl-Meyer Assessment for upper extremity (FMA-UE); muscle power threshold, measured with a grip algometer; and self-reported degree of pain [Visual Analogue Scale (VAS) score].

Upper limb function will be assessed with the FMA-UE, a stroke-specific test for measuring motor impairment and recovery (31). The FMA-UE, which is widely used to evaluate upper limb motor function in patients with stroke, is often applied in studies of pain disorders in the upper extremities (32). The maximum score of the upper extremity scale is 66 points, divided among three components: shoulder–arm (36 points), wrist–hand (24 points), and coordination (6 points). The reliability and validity of the FMA-UE are excellent, and it is sufficiently sensitive for both clinical and research applications (33). The assessment will be performed in a standardized manner to differentiate the function levels of the fistula and non-fistula arms.

Handgrip strength will be measured with a digital handgrip dynamometer (TTM-YD, Tokyo, Japan). Two consecutive measurements of the fistula-side hand will be performed at an interval of 30 s, and the maximal isometric reading will be used for data analysis (34). Hand strength is used as a simple metric of general muscle strength for identifying functional deficits (35). It can also provide good resolution for localized pathologies and provides outcomes that allow better understanding of the therapeutic response of the impaired hand (36).

Pain perception will be recorded immediately after cannulation on a VAS, a non-graduated horizontal line of 100 mm where 0 = no pain at all and 100 = as painful as possible. The VAS and grip strength measures will be assessed immediately before the first treatment; at 4, 6, and 10 weeks after the first treatment; and at follow-up.

### Safety assessments

Juan Bi Tang is described in the ancient literature of TCM as relatively safe, and previous clinical studies have reported no major toxicity in therapeutic doses (37–39). However, we will still perform a series of measures to assess the safety of JBT throughout the entire trial due to possible herb-induced toxicity or herb-dialysis interaction (40). All safety-related variables, including vital signs, physical examination, hematological test, biochemical test, and AEs, will be recorded in the case report at every visit. Laboratory testing of the participants' blood, electrolytes (i.e., potassium, phosphorus, and calcium), albumin, parathyroid hormone, and kidney and liver function will be monitored before the intervention, at 2-week intervals during the intervention, and again at 2 weeks after trial completion. In addition, all details of AEs and other ailments will also be documented accurately at every study visit, including the occurrence time, severity, duration, effective measures, and transfer. Each AE associated with the intervention drugs will be classified as mild, moderate, or severe. If severe AEs such as hyperkalemia, thrombocytopenia, liver injury, bleeding, or cardiovascular events related to JBT occur during the study, the principal investigator will provide immediate diagnosis and treatment and report the AE to the Institutional Review Board within 24 h of the time of recognition. All AEs will be monitored and recorded by an independent researcher unassociated with the study until recovery of the participant.

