**Figure 1 F1:**
[figure not shown]
Study design from enrollment to analysis following the CONSORT 2010 flow diagram.

**Table 1 T1:** Summary of collected data at each time point according to SPIRIT 2013 guidelines.

**Testing variables**	**Screening**	**Randomization**				**Follow-up**
	**Week 1**	**Week 0 (baseline)**	**Week 4**	**Week 6**	**Week 10**	**Week 12**
Inclusion and exclusion criteria	X					
Baseline information	X					
Inform consent	X					
Intervention						
Period I		X	X			
Period II				X	X	
Assessment						
VAS		X	X	X	X	X
KDQOL-36		X	X	X	X	X
FMA-UE		X	X	X	X	X
Griping force		X	X	X	X	X
Laboratory data		X	X	X	X	X
Conditional information			X	X	X	
Adverse events			X	X	X	X

VAS, visual analog scale; KDQOL-36, Kidney Disease Quality of Life 36-Item Short-Form Survey; FMA-UE, Fugl-Meyer Assessment for upper extremity.

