### Study participants

Participants will be recruited from Kaohsiung CGMH via posters and advertisements on the official hospital website. The recruitment period is planned to last 18 months. All participants will provide informed consent before randomization. The schedule of patient enrollment, intervention, and assessment is illustrated in Table 1.

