### Interventions

The CHM product investigated in this study will be prescription-grade JBT powder (Product code; NO.0321131, Ko Da Pharmaceutical Co., Ltd., Taoyuan, Taiwan) manufactured in accordance with Good Manufacturing Practices (GMP) and tested before factory release. Juan Bi Tang consists of 4 g *Rx. Angelica Sinensis*當歸, 4 g *Rx. Paeoniae Rubra*赤芍, 4 g *Rx. Astragali*黃耆, 4 g *Rz. Curcuma Longae*薑黃, 1 g *Rx. et Rz. Notopterygii*羌活, 4 g *Rx. Saposhnikoviae*防風, 3 g *Rz. Zingiberis Recens*生薑, 2 g *Fr. Zizyphi Jujube*大棗, and 1.5 g *Rx. Glycyrrhizae Preparata*炙甘草. These raw herb materials, together with starch excipient, are extracted and concentrated according to a standardized Chinese formula (see: http://www.koda.com.tw/tqm04_e.aspx). The participants will be instructed to take JBT orally in doses of 3 g (per bag) each time, thrice daily, for 4 weeks. Patients will return each week to the outpatient clinic for evaluation, medication, and counting of any unconsumed bags. Weekly compliance below 75% will be considered a deviation from the protocol and will lead to exclusion from further participation in the study. Participants in the non-treatment period will receive simple self-care measures for MPS based on the non-pharmacologic intervention in patients with CKD by Pham et al. (18). These will mainly include physical activities such as stretching, aerobic and strength exercises, and some types of combined exercises (18). The duration of the intervention will be 8 weeks, and the follow-up will be at 2 weeks.

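### Laboratory safety tests are two-weekly in the text, but Table 1 has none at weeks 2 and 8; whether weekly visits, and so adverse event enquiry, cover the non-treatment period is not stated

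*Protocol article*

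**What the plan says.** Four places in the protocol article bear on when safety data are collected.

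- **Safety assessments, timing sentence.** Blood, electrolytes, albumin, parathyroid hormone, and kidney and liver function are tested before the intervention, "at 2-week intervals during the intervention, and again at 2 weeks after trial completion".
- **Safety assessments, recording sentence.** Just before that, the safety variables, "including vital signs, physical examination, hematological test, biochemical test, and AEs, will be recorded in the case report at every visit". The section later repeats that adverse events (AEs) are documented at each study visit.
- **Table 1 (under Study design).** Its title is "Summary of collected data at each time point according to SPIRIT 2013 guidelines". The row "Laboratory data" is marked at weeks 0, 4, 6, 10 and 12. The AE row is marked at weeks 4, 6, 10 and 12, without distinction by sequence. There is no column for any week within a 4-week period. The Study participants section points to this table: "The schedule of patient enrollment, intervention, and assessment is illustrated in Table 1".
- **Interventions.** Between the JBT dosing instruction and the weekly compliance rule stands: "Patients will return each week to the outpatient clinic for evaluation, medication, and counting of any unconsumed bags". For the other period the section says: "Participants in the non-treatment period will receive simple self-care measures for MPS", with no visit frequency. It gives the length of the intervention as 8 weeks.

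**The concern.** The two-weekly rule and Table 1 cannot both be followed. Staff working from the table would take no blood between the first and last day of a 4-week JBT course. Staff working from the text would take it once in the middle. The Safety assessments section gives possible toxicity and interaction with dialysis as the reason for monitoring, and lists raised potassium, low platelets and liver injury among the severe events. The Subject withdrawal criteria include worsening electrolyte disorders. Whether a laboratory change could be picked up part-way through a course therefore depends on which passage is read.

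The second matter is ascertainment. AEs are recorded at visits, so the number of visits in a period sets how often they are sought. Medication supply and bag counting, two of the three stated purposes of the weekly visits, have no object when no drug is given, which suggests that these visits belong to the JBT period. If so, the period with more enquiry will tend to show more events, whatever the treatment does. The trial is open-label, so blinding offers no protection.

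**Working it through.** **The calendar.** Study design and Interventions give 4 weeks (period I), 2 weeks of washout, 4 weeks (period II) and 2 weeks of follow-up: 4 + 2 + 4 + 2 = 12 weeks, as the article states. Period I runs from week 0 to week 4 and period II from week 6 to week 10.

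**Laboratory tests under each statement.** The last column counts tests after the start of a 4-week period, up to and including its end.

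| Statement followed | Weeks tested | Tests per participant | Tests per 4-week period |
|---|---|---|---|
| Table 1 | 0, 4, 6, 10, 12 | 5 | 1 |
| Two-weekly sentence | 0, 2, 4, 6, 8, 10, 12 | 7 | 2 |
| Every visit, weekly visits in both periods | 0, 1, 2, 3, 4, 6, 7, 8, 9, 10, 12 | 11 | 4 |
| Every visit, weekly visits on JBT only | group A: 0, 1, 2, 3, 4, 6, 10, 12; group B: 0, 4, 6, 7, 8, 9, 10, 12 | 8 | 4 on JBT, 1 off |

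**Differences.**
- The two-weekly schedule minus Table 1 leaves weeks 2 and 8: 7 − 5 = 2 tests per participant, or 40 × 2 = 80 across the planned 40 participants if all complete.
- The longest gap between tests within a period is 4 weeks under Table 1 and 2 weeks under the sentence.
- The weekly visits fall at weeks 1, 2, 3, 4 and 7, 8, 9, 10 if held in both periods. Six of these (weeks 1, 2, 3, 7, 8, 9) are not in Table 1, and four (weeks 1, 3, 7, 9) are not in the two-weekly schedule.

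**Does a narrower reading remove the conflict?**
- If a visit means only a Table 1 visit, the every-visit sentence agrees with the table, but the two-weekly sentence still does not.
- If the intervention means only the JBT course, each participant still needs one test that Table 1 lacks: week 2 in group A, week 8 in group B.
- Neither reading makes the text and the table agree.

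**AE contacts per 4-week period, counted in the same way.**

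| Reading | On JBT | Off JBT |
|---|---|---|
| Table 1 visits only | 1 | 1 |
| Weekly visits in both periods | 4 | 4 |
| Weekly visits on JBT only | 4 | 1 |

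The article does not settle which row applies.

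**The case against.** The strongest reply is that only one mismatch is certain, and that the rest depends on how the sentences are read. Most of this is fair.

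- **Weekly visits.** A reader might infer that AE capture is unequal as the plan is written. The documents do not establish that. The weekly-visit sentence is not limited to one period, its first purpose is evaluation, and the AE row of Table 1 treats both sequences alike. The 4 to 1 ratio is conditional.
- **Laboratory bias.** A reader might also infer that laboratory results are collected unequally on and off JBT. Neither explicit laboratory schedule supports that. Table 1 gives one test per period, and the two-weekly rule over an 8-week intervention gives two. Inequality needs further assumptions, such as counting weekly visits as visits and confining them to JBT.
- **Withdrawal.** It would go too far to say that withdrawal for electrolyte disorders rests on tests missing from the schedule. Table 1 has tests at weeks 4, 6, 10 and 12, and the text names potassium, phosphorus and calcium. Only the mid-period tests are in doubt.
- **The every-visit sentence.** It may govern what is entered in the case report rather than when blood is drawn. On that reading it adds no conflict.

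One part does not stand. Table 1 is called a summary, but that does not excuse the omission. The text sends the reader there for the assessment schedule, and the laboratory row names specific weeks. The trial is at a single centre, so inconsistency between sites is not the risk. Staff still need one schedule.

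**Conclusion.** The laboratory contradiction holds. The two-weekly sentence requires tests at weeks 2 and 8 that Table 1 does not contain, so under the table no safety test falls within either 4-week period. This rests on counting two-week intervals from the start of each period and on the stated 8-week intervention. If the intervention meant JBT alone, one test per participant would be missing instead of two.

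The conflict with the every-visit sentence is conditional on weekly visits counting as visits. The AE point is conditional too: if weekly visits are held only on JBT, AEs are sought four times against once, and the comparison would lean towards finding more events on JBT. How far it would shift the observed rates cannot be worked out from the document. The article leaves the condition open, and that should be corrected. No sample size or power figure is affected. Which laboratory frequency is appropriate is not judged here.

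**What to change.** Reconcile Table 1, Interventions and Safety assessments to a single laboratory and visit schedule, and give Table 1 a column for every week in which a test or visit is planned. No frequency is proposed here; that is for the investigators to settle. Say what counts as a visit for the laboratory and AE rules, and whether the weekly visits take place in the non-treatment period.

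Then state that the same laboratory schedule and the same AE enquiry apply in the JBT and non-treatment periods of both sequences. Participants attend dialysis three times a week under the inclusion criteria, so those sessions could carry the AE enquiry without extra attendance. If they are used, they must be used equally in both periods; using them only off JBT would create the opposite imbalance.

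The cost is a correction of table and text, plus slightly more AE recording in the non-treatment period.

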### Statistical analysis

#### Sample size

A statistical power analysis by G^*^Power version 3.1.9.2 for the differences in the outcome measure between both groups was conducted to determine the investigated sample size to achieve adequate power (80%, α = 0.05). For repeated measures ANOVA analysis, to achieve 80% power and a 25% effect size (40), at least 34 participants will be needed. Considering a 15% loss to follow-up, we plan to recruit 40 participants (20 participants for each group) to compensate for possible dropouts.

#### Data analyses

Both intention-to-treat (ITT) and per-protocol (PP) analyses will be applied in the present trial. Continuous data will be presented as mean ± SD, and categorical data will be presented as frequencies and proportions. The Student's *t*-test for continuous variables and chi-squared test for categorical variables will be used to compare the characteristics and clinical data of patients with and without JBT treatment. Repeated measures ANOVA will be conducted to compare the subjects' conditions over time. The Mann–Whitney U test and generalized estimating equation will be applied to compare differences when the distribution of data does not meet the assumption of normality. All analyses will be performed in IBM SPSS Statistics 22 (IBM Co., Armonk, NY, USA). A *p*-value <0.05 will be considered statistically significant.

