#### Subject withdrawal criteria

Study participation will be terminated under the following conditions:

Occurrence of severe complications and/or general health deterioration (i.e., sepsis, bleeding, AV fistula occlusion, and progress of electrolyte disorders such as ECG change of hyperkalemia, or uncontrolled calcium × phosphorus (Ca × P) level);Occurrence of a severe adverse event (AE) of any type during the intervention;Voluntary withdrawal from the trial, absence from two consecutive interviews, or loss to follow-up.

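### The default longitudinal method, repeated measures ANOVA, does not deliver the promised intention-to-treat analysis unless missing values are imputed

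*Protocol article*

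**What the plan says.** Under Data analyses, the article commits to two analyses: "Both intention-to-treat (ITT) and per-protocol (PP) analyses will be applied in the present trial". The method for outcomes over time follows: "Repeated measures ANOVA will be conducted to compare the subjects' conditions over time". A fallback is named beside the Mann–Whitney test: "generalized estimating equation will be applied to compare differences when the distribution of data does not meet the assumption of normality". Its trigger is the shape of the distribution, not missing visits. The software is fixed: "All analyses will be performed in IBM SPSS Statistics 22". A t-test comparing patients with and without JBT is also listed.

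The plan expects patients to leave. Under Sample size: "Considering a 15% loss to follow-up, we plan to recruit 40 participants", after the statement that "to achieve 80% power and a 25% effect size (40), at least 34 participants will be needed".

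Under Subject withdrawal criteria, "Study participation will be terminated under the following conditions" introduces a list that includes severe complications, general deterioration, severe adverse events, voluntary withdrawal and loss to follow-up. The Interventions section adds another exit: weekly compliance under 75%, judged by counting unused bags, excludes the patient from the rest of the study.

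Outcome measurement schedules five assessments, at weeks 0, 4, 6, 10 and 12.

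**The concern.** An intention-to-treat analysis should keep every randomised patient, whatever happens after randomisation. Classical repeated measures ANOVA needs a full set of the measurements entered and deletes the whole patient if one is absent. With normally distributed outcomes and some missing visits, the plan as worded selects the method that discards patients, and withholds the named method that could use their partial data.

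The exits are unlikely all to be unrelated to treatment. Bags are counted only when there are bags to count, so the compliance exit operates only during JBT. Those are patients an ITT analysis should retain and a per-protocol analysis would drop. If the ANOVA drops them too, the two analyses rest on nearly the same patients and the ITT result is a weak check on the per-protocol one.

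The crossover adds a cost. A group A patient who leaves after week 4 has already supplied a complete JBT period. If the model covers both periods, those data go unused.

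**Working it through.** **1. The plan's own figures.** Inputs from Sample size: effect size 25%, read as f = 0.25; α = 0.05; power 80%; loss 15%. The number of measurements m and their correlation ρ are not stated; I assume m = 2 and ρ = 0.5. For the within-subject effect, or the group-by-time interaction with two groups:

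- λ = f² × N × m / (1 − ρ) = 0.0625 × 34 × 2 / 0.5 = 8.5, on 1 and 32 degrees of freedom. Power is 0.807, and N = 34 is the smallest even total reaching 80%.
- Recruitment: 34 / 0.85 = 40.

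Both stated figures reproduce. With m = 4 or m = 5 the formula gives 24 or 22, so the 34 fits two measurements, not five.

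**2. What the default method uses.** At the planned loss, 40 × 0.85 = 34 patients are analysed and 6 are left out. If all six left after week 4, each would have given 2 of 5 visits, so a model over all visits would discard 6 × 2 = 12 observed assessments. The article does not say whether the 15% includes the compliance exclusions.

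**3. Power.** With 40 complete patients λ = 0.0625 × 40 × 2 / 0.5 = 10 and power is 0.869, against 0.807 with 34. The loss is already budgeted.

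**4. Bias under one assumed mechanism.** The article gives no dropout mechanism, so this is an illustration. Assume standardised outcomes (SD 1, higher is better) and correlation 0.5 between any two visits, so a change between two visits has SD √(2 × 0.5) = 1. In each group the worst-changing 15% (3 of 20) leave: group A after week 4, judged on the change from week 0 to 4; group B before week 10, judged on the change from week 0 to 6. Removing the lowest 15% shifts the mean of the selecting variable by φ(z₀.₁₅) / 0.85 = 0.274. Other quantities shift by 0.274 times their covariance with it.

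*End-of-period scores, JBT minus no treatment:*
- Group A (week 4 minus week 10): week 4 shifts by (1 − 0.5) × 0.274 = 0.137; week 10 by (0.5 − 0.5) × 0.274 = 0. Contrast +0.137.
- Group B (week 10 minus week 4): both covariances are 0.5 − 0.5 = 0. Contrast 0.
- Average: 0.137 / 2 = 0.069 SD.

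Simulation of 10,000 trials agrees: completers give 0.066 for a true effect of 0 and 0.564 for a true 0.50. In a separate run of 2,000 trials, a model on all available visits gave 0.002 and 0.501.

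*Within-period changes, JBT minus no treatment, same mechanism:*
- Group A: the JBT change shifts by 1 × 0.274; the untreated change (week 6 to 10) by 0. Contrast +0.274.
- Group B: the JBT change has covariance −0.5 with the selecting change, a shift of −0.137; the untreated change has covariance +0.5, a shift of +0.137. Contrast −0.274.
- Average: 0. Simulation gives 0.000 and 0.500.

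If both groups are instead judged on the change from week 0 to 4, the end-of-period contrast is also unbiased (simulated −0.001 and 0.502).

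**The case against.** The best defence is that ITT and repeated measures ANOVA coexist once missing values are imputed. An imputation rule is commonly left to a fuller plan, which is not shown. That stands: the absence of a rule in this article is not a fault, and the point has to be conditional on no imputation.

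A reader might infer that any missed visit removes a patient. The documents do not support this. Only measurements entered in the model count, the article does not say which those are, and the sample size fits two. A patient missing only week 12 need not be lost.

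A reader might also infer that nothing in the plan can use partial data. The t-test needs no full set of visits, GEE is named, and the Discussion provides for a first-period analysis if carry-over occurs, in which someone leaving later still counts. These are real, but none is the default analysis over time when data are normal, and none is triggered by missing visits.

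Finally, a reader might conclude that the JBT effect will be inflated, by 14% on a true 0.50 SD (0.07 / 0.50). That figure belongs to one group-specific mechanism and one estimator, and vanishes under the alternatives shown. Reasons such as sepsis, fistula occlusion or loss to follow-up can arise in either period without reflecting response to JBT.

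**Conclusion.** The point holds in limited form. As worded, the default analysis over time leaves out randomised patients whom an ITT analysis should keep, unless missing values are imputed. At the plan's own loss rate that is about 6 of 40, some of them potentially for reasons tied to JBT, and the result comes close to the per-protocol analysis. The fault lies in pairing an ITT promise with a complete-case method while tying the partial-data method to non-normality.

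It does not follow that ITT must become a completer analysis, because imputation is not ruled out. Nor is any size or direction of bias established: the range shown is 0 to about 0.07 SD, on assumed mechanisms with correlation 0.5. Power is not at issue (about 0.81 with 34, under the assumed m = 2 and ρ = 0.5). The change is worth making because it is nearly free and restores the purpose of running two analyses.

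**What to change.** In Data analyses, define the ITT analysis of each continuous outcome as a linear mixed model (SPSS MIXED) on all available visits of all randomised patients, with a random patient effect and fixed effects for visit or period and for JBT exposure. GEE used regardless of normality is an alternative. State that period I data of patients who leave later are included. Keep the complete-data analysis for the per-protocol set only.

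The cost is a change of wording in the same software, with no extra patients or visits and no new sample size. There are two downsides. The mixed model is valid only if data are missing at random given what was observed, and GEE needs a stricter assumption; neither can recover outcomes that were never collected. The ITT estimate may also be slightly less favourable than the complete-data one.

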The strengths of this study include: (1) This study is the first pilot randomized cross-over trial to evaluate the feasibility of JBT for the treatment of dialysis-related myofascial pain. (2) The design of the trial is based on TCM syndromes because dialysis-relayed myofascial pain can be inferred to inadequate *qi* and blood around the fistula arm in patients receiving hemodialysis. (3) The study of different safe and lower cost can be considered for scientific use of techniques related to TCM in dialytic patients. Nevertheless, a few study limitations should be noted. First, this study will be an open-label study because of the difficulty of preparing a suitable placebo; the pharmaceutical technology of CHM powder does not yet allow such a process because of the distinctive colors, tastes and smells of the preparations (51). Moreover, due to the use of patient-reported outcomes, the reliability of the conclusions of the study may be reduced due to the absence of participant blinding. Second, it will be a crossover trial and thus may entail possible carryover effects. The component of JBT with the longest half-life is *Rx. et Rz. Notopterygii* (*T*_1/2_ = 190–768 min); however, its washout period is only 64 h (52). To minimize this possibility, we have designed a 2-week washout period between the two groups. However, no data on the length of the washout period of JBT are currently available. The washout period involves the biological half-lives of multiple herbs and changes in the pharmacokinetics of the CHM formula (53). In the event of carry-over effects, only data from the first period will be used for the analysis, for it is a randomized parallel-group design. The current sample size was calculated on the basis of a single period of data alone; thus, the estimated size will be sufficient for specific analysis. Third, the non-treatment and JBT treatment periods will be only 4 weeks.

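### The named analyses do not use the week-0 score as a covariate, which costs precision in any first-period (week-4) comparison of the two groups

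*Protocol article*

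**What the plan says.** The Primary outcome section states: "The primary outcome used in this study will be the Kidney Disease Quality of Life 36-Item Short-Form Survey (KDQOL-36". Under Outcome measurement, "The subjects will be assessed five times: prior to the study, at 4 weeks (at the end of period I", then "at 6 weeks (at the beginning of period II), at 10 weeks (at the end of period II", and at a follow-up visit. Table 1 marks KDQOL-36, VAS, FMA-UE and grip force at weeks 0, 4, 6, 10 and 12. Every outcome therefore has a score from before the first treatment period.

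The Data analyses section names a Student's t-test for continuous variables and a chi-squared test for categorical ones; these "will be used to compare the characteristics and clinical data of patients with and without JBT treatment". It then says "Repeated measures ANOVA will be conducted to compare the subjects' conditions over time". A Mann–Whitney U test and a generalized estimating equation are held in reserve for non-normal data. No covariate is named for any of these, and the section does not say which visits enter the ANOVA.

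The Discussion, among the limitations, says that if carry-over occurs, "only data from the first period will be used for the analysis, for it is a randomized parallel-group design". It adds that the sample size was calculated from a single period, and that no data on the washout length of JBT are available. The Sample size section gives the design values: a calculation "to achieve adequate power (80%, α = 0.05", and, for repeated measures ANOVA, "to achieve 80% power and a 25% effect size (40), at least 34 participants will be needed". After 15% loss this becomes 40, or 20 per group.

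**The concern.** A first-period comparison sets 17 to 20 patients per group against each other. The pairing that makes a crossover efficient is gone, and the patient's own week-0 score is the main remaining way to reduce noise. Neither named test makes full use of it.

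- A t-test on week-4 values ignores week 0. A chance difference between the groups at week 0 then passes into the estimated effect to the extent that the two scores are correlated.
- A group-by-time ANOVA on weeks 0 and 4 is equivalent to a t-test on change scores. It uses the baseline, but subtracts all of it instead of the share that regression would assign. When the correlation is 0.5, this gives no gain over ignoring the baseline.

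At stake is power in the analysis on which the trial says it was sized, and which it would rely on if carry-over appeared.

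**Working it through.** **Inputs from the article.** α = 0.05 (two-sided assumed), effect size 0.25 (read as Cohen's f), 34 patients needed, 40 recruited, two equal groups.

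**Inputs not in the article, assumed.** Two measurements per patient, equal variance at both visits, and correlation ρ between them. I take ρ = 0.5 as the reference and show 0.3 to 0.7.

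**Step 1: reproduce the planned 34.** For the group-by-time interaction with m = 2 measurements, the noncentrality is λ = N·f²·m/(1−ρ) = 34 × 0.0625 × 2/0.5 = 8.5. On F(1, 32) this gives power 0.807, and 34 is the smallest even N that reaches 80%. At N = 40 the power is 0.869. Inflating 34 for 15% loss gives 34/0.85 = 40. This is the simplest set of assumptions that returns 34, but not the only one: a between-groups test with four measurements and ρ = 0 also does.

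**Step 2: express f as a group difference.** For a change-score t-test, λ = (N/4)·D²/[2(1−ρ)], where D is the difference in change in SD units of the outcome. Equating this with Step 1 gives D² = 8·m·f² = 8 × 2 × 0.0625 = 1, so D = 1.0 SD whatever ρ is.

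**Step 3: compare the three analyses of week 4.** With the outcome variance set to 1, the variances are:

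- t-test on week-4 values: 1
- change score (group-by-time): 2(1−ρ)
- ANCOVA on week 0: 1−ρ², with one degree of freedom fewer

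At ρ = 0.5 these are 1, 1 and 0.75. Since 1−ρ² = (1−ρ)(1+ρ) and 1+ρ ≤ 2, the ANCOVA variance never exceeds either of the others. Power from the noncentral t distribution at D = 1.0 SD:

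| N | ρ | Week-4 t-test | Change score | ANCOVA | Gain over t-test (points) | Gain over change score (points) |
|---|---|---|---|---|---|---|
| 34 | 0.3 | 80.7% | 66.6% | 84.1% | 3.4 | 17.5 |
| 34 | 0.5 | 80.7% | 80.7% | 90.3% | 9.6 | 9.6 |
| 34 | 0.7 | 80.7% | 95.4% | 97.7% | 17.0 | 2.3 |
| 40 | 0.3 | 86.9% | 74.0% | 89.8% | 2.9 | 15.7 |
| 40 | 0.5 | 86.9% | 86.9% | 94.5% | 7.6 | 7.6 |
| 40 | 0.7 | 86.9% | 97.8% | 99.1% | 12.2 | 1.2 |

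The two gains run in opposite directions: a higher ρ widens the gap to the t-test and narrows the gap to the change score. Extending ρ to 0.8, ANCOVA is still highest at both sample sizes, but its lead over the change score falls to 0.3 points at N = 34.

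**Step 4: the two-period contrast.** Here the outcome is the within-patient difference Y4 − Y10 and the candidate covariate is Y0 − Y6. If all visits are equally correlated, their covariance is ρ − ρ − ρ + ρ = 0, so adjustment gains nothing and costs one degree of freedom. For a 0.5 SD effect, ρ = 0.5 and N = 34, power is 80.7% without adjustment and 80.6% with it. If the correlation instead decays with time (0.3 to 0.8 per four weeks), the gain is about 0 to 2 points.

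**The case against.** Four objections deserve weight.

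*The baseline may already be used.* If week 0 is a level of the repeated measures ANOVA, the group-by-time term does use it, and a chance week-0 difference is not carried forward as it is in a t-test on week-4 values. This stands. A reader might infer that every named analysis ignores the baseline; the text does not support that. What remains is that the change score uses the baseline less efficiently, by 1 to 2 points at ρ = 0.7 and 16 to 17.5 points at ρ = 0.3. Nor does the article say that its t-test will be run on week-4 values.

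*The trial is a crossover.* A reader might infer that its main within-patient comparison also loses 8 to 10 points, and that the week-6 score should be a covariate too. Neither follows. Step 4 shows almost no gain, and the week-6 score is taken after randomization and may itself contain carry-over. The point is confined to single-period comparisons, and the fallback in the Discussion applies only if carry-over occurs.

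*The correlation is assumed.* This stands. Any single figure must be given with its ρ.

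*Covariates are often left to a statistical analysis plan, and this is a condensed article that describes the trial as a pilot.* This is fair, and silence alone would be no finding. But the article does name its tests, and an analysis plan that used ANCOVA would have to be reconciled with them.

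**Conclusion.** The point holds for any comparison of the two groups within one period, including the first-period fallback. It is a free gain in efficiency: the named tests are valid and unbiased under randomization, and nothing in the article is false on this point.

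The reference size, 9.6 points of power at 34 patients and 7.6 at 40, rests on four assumptions: ρ = 0.5, equal variances, a two-sided test, and f = 0.25 read as a 1.0 SD difference in change. For ρ from 0.3 to 0.7 the gain over a week-4 t-test is about 3 to 17 points, and over the group-by-time test about 1 to 17.5 points. The direction does not depend on ρ: ANCOVA was the most powerful of the three in every case computed from 0.3 to 0.8.

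**What to change.** Add to the Data analyses section that any first-period comparison of KDQOL-36 scores and of each secondary outcome will use ANCOVA of the week-4 score on randomized group, with the week-0 score as covariate, in place of the t-test or the group-by-time ANOVA. Leave the two-period within-patient contrast without the week-0 and week-6 period baselines as covariates.

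The cost is one sentence and one degree of freedom. The week-0 scores are already scheduled, so no visit, measurement or patient is added.
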